**Methods:**

The cost-effectiveness of MST will be assessed through a Randomised Controlled Trial. Primary outcomes aggressive and delinquent behaviour will be assessed with the parent-reported CBCL and adolescent-reported YSR. Health care utilisation, production loss, and quality of life are recorded using the self-report 'Trimbos and iMTA questionnaire on Costs associated with Psychiatric illness' (TiC-P), and with the MOS Short-Form General Health Survey (SF-20) and EuroQol -5D (EQ-5D), respectively. The study aims to enrol 100 clients in both conditions (MST and CAU). Data will be obtained before treatment (T1), immediately after treatment (T2; 5 months after T1) and at follow up (T3; 6 months after the end of the treatment) from a variety of sources, i.e. clients, parents/primary carers, professionals and police records.

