### Interventions

**MST**. Multisystemic Therapy (MST) is an intensive, short-term, home- and community- based intervention program for families of youth with severe psychosocial and behavioural problems. It is based on the social ecological theory of Bronfenbrenner [15] and on models of the cause of delinquency [16]. MST is designed to address complex psychosocial problems and provides an alternative treatment for out-of-home placement of children and youth. It uses the various systems in which the adolescent is embedded: family, peer group, school and neighbourhood. In consultation with the members of the family, the therapist identifies a set of treatment goals and assigns the tasks required to accomplish these goals. MST lasts 4 to 6 months and takes the individual needs of the client into account. Therapists are available 7 days a week, 24 hours a day. Each team includes 3–5 therapists who have a caseload of 3–5 clients each.

**CAU**. Care-As-Usual consists of treatments that are already available for adolescents with severe psychosocial and behavioural problems: juvenile justice services, child welfare services, individual adolescent counselling and home-based social services (for instance, parental counselling). Also included and variably implemented across regions are recently developed, evidence-based services such as Functional Family Therapy (FFT) [17] and Multi-Dimensional Family Therapy (MDFT) [18].

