### Randomization

Immediately after referral (Western part of the Netherlands) or after the residential period (Northern part of the Netherlands), participants will be randomized to MST or CAU with the use of a computerized randomization program. This program will execute the randomization separately for each site. The ratio of randomization between MST and CAU will be 1:1.

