### Data collection procedure

Data will be collected using a standardized self-report questionnaire in a face-to-face situation. The questionnaires will be administered before the intervention (T1), directly after the intervention (T2) and six months after the intervention (T3). Adolescents and their parents will both receive €10 for filling out the questionnaire. The therapist will fill out a questionnaire after the treatment has finished (T2). The questionnaires are also available in old Berber for the Berber Moroccan families. In addition, we make use of one Arab translator who will visit all Arab families.

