### Statistical analysis

First, descriptive statistics will be performed to describe the demographic characteristics of the study population.

Second, primary measures of effect will be analysed using within group comparisons (pre-post treatment) and between group comparisons. The latter one will use difference scores (pre-post intervention) after which the treatment effects of the two treatment conditions will be compared. Statistical testing will be done using either the paired t-test or the Wilcoxon signed-rank test for comparisons within the treatment groups and the unpaired t-test or the Mann–Whitney U test for comparisons between the treatment groups.

Third we will describe the mean costs per respondent in both treatment groups. Differences in costs between the intervention group and the control group will presented based on the trial data, and 95% confidence intervals will computed based on bootstrap re-sampling with 5000 replications of the trial data. Separate estimates will be made for different cost categories. For the cost-effectiveness analysis, mean annual societal costs will be linked to the primary measure of effect (Aggressive behaviour and Delinquent behaviour). A cost utility analysis will link the EQ-5d based utilities to the cost.

Fourth, point estimates for the incremental cost-effectiveness and cost utility ratio (ICER) will be computed on complete cost-effect pairs by dividing the incremental societal costs by the incremental effects at 12 months. Uncertainty around the ICERs will be estimated using bootstrapping, generating 5000 replications of the original dataset. A cost-effectiveness acceptability curve (CEAC) will be generated to represent the probability that MST is cost-effective compared to usual care over a range of thresholds [26,36].

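### The arms are compared on unadjusted pre-post change scores, without the T1 score or site in the model, while the ICER uses the 12-month effect, for which no between-group comparison is described

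*Protocol article*

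**What the plan says.** The relevant statements in the protocol article are these.

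- **Effect variable** (Statistical analysis): "The latter one will use difference scores (pre-post intervention) after which the treatment effects of the two treatment conditions will be compared".
- **Test** (Statistical analysis): "the unpaired t-test or the Mann–Whitney U test for comparisons between the treatment groups". The section names no covariate and no site term.
- **Randomisation** (Randomization): "This program will execute the randomization separately for each site". Under Recruitment there are three institutions. In the North, randomisation follows a secure residential period and usual care is FFT. In the West, families come through several kinds of referrer.
- **Effect in the ICER** (Statistical analysis): obtained by "dividing the incremental societal costs by the incremental effects at 12 months". Under Costs items, the cost horizon is one year.
- **Visits** (Abstract, Methods): "immediately after treatment (T2; 5 months after T1) and at follow up (T3; 6 months after the end of the treatment". Data collection procedure gives the same order: "before the intervention (T1), directly after the intervention (T2) and six months after the intervention (T3".

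**The concern.** Two features of the stated analysis fit the design poorly.

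**Different quantities.** The effect test and the ICER do not address the same quantity. The test looks at change from before to after the intervention, which by the article's own labels is T1 to T2. The ICER uses the effect at the end of follow-up. If an effect present at T2 fades or grows by T3, the effectiveness statement and the economic statement can point in different directions, and the article describes no between-group estimate that links them. The Mann–Whitney option widens the gap. It does not test the mean difference, whereas the ICER and the acceptability curve are built on mean differences.

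**Discarded information.** The comparison does not use information that the trial collects anyway. A change score fixes the coefficient of the T1 score at 1 instead of estimating it, and it carries a chance imbalance at T1 into the result through regression to the mean. Site is left out although allocation is balanced within site. The cost is precision.

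**Working it through.** **1. Time points.** T1 = 0 and T2 = 5 months. T3 = 5 + 6 = 11 months. With treatment lasting 4 to 6 months (Interventions), T3 falls at 4 + 6 = 10 to 6 + 6 = 12 months. The 12-month effect can therefore only be the T3 measurement, while post-intervention is T2. That the tested interval is T1–T2 is an inference, but both descriptions of the visits support it.

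**2. The plan's own figure.** The inputs from Sample size are power 0.80, alpha 0.05 (two-sided assumed) and a medium effect (taken as d = 0.5). Then n = 2(1.960 + 0.842)²/0.5² = 62.8, so 63 per arm by the normal approximation. The noncentral t gives 63.8, so 64. The stated 64 reproduces. The enrolment target is 100 per arm.

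**3. Baseline adjustment.** Let ρ be the correlation between T1 and the later score, with equal SDs σ at both visits. The article does not give ρ, so a range is assumed.

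- Residual variance of the change score: 2(1−ρ)σ²
- Residual variance under ANCOVA: (1−ρ²)σ²
- Ratio: (1−ρ²)/[2(1−ρ)] = (1+ρ)/2

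Power ≈ Φ(d√(n/2)/√v − 1.96), where v is the residual variance in units of σ². With n = 100 and d = 0.5 on the raw-score SD (assumed), d√(n/2) = 0.5 × √50 = 3.536.

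| ρ | v, change | v, ANCOVA | Ratio | Power, change | Power, ANCOVA | n per arm for 80%, change vs ANCOVA |
|---|---|---|---|---|---|---|
| 0.3 | 1.40 | 0.91 | 0.65 | 0.848 | 0.960 | 88 vs 58 |
| 0.5 | 1.00 | 0.75 | 0.75 | 0.942 | 0.983 | 63 vs 48 |
| 0.7 | 0.60 | 0.51 | 0.85 | 0.995 | 0.999 | 38 vs 33 |

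Worked entry at ρ = 0.3, change score: 3.536/√1.40 = 2.988; 2.988 − 1.96 = 1.028; Φ(1.028) = 0.848. Below ρ = 0.5 the change-score variance exceeds σ², so the change score is then less precise than the later score alone.

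**4. Site.** Suppose site explains a share s of outcome variance and allocation is balanced within site. The unadjusted test then uses a variance too large by a factor 1/(1−s). At an assumed s = 0.10 the real type I error is 2[1 − Φ(1.96/√0.9)] = 2[1 − Φ(2.066)] = 0.039. A simulation of 6,000 runs, with three sites of assumed size 80, 60 and 60, agrees:

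| Site share (assumed) | Type I error, site omitted | Power at d = 0.4, site omitted | Power at d = 0.4, site in model |
|---|---|---|---|
| 5% | 0.047 | 0.813 | 0.827 |
| 10% | 0.040 | 0.816 | 0.843 |
| 20% | 0.026 | 0.818 | 0.869 |

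With site in the model, type I error was about 0.05 throughout.

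**The case against.** The best defence is that nothing here invalidates the trial. Under 1:1 randomisation the change-score comparison is unbiased, and at 100 per arm its power is above the stated 80% at every ρ shown. If d = 0.5 is meant on the scale of the difference score itself, 64 per arm gives 80% as stated. An unseen analysis plan may also add adjusted analyses. All of this stands, and it limits the size of the point. It does not remove it, because the article fixes the change score, the tests and the ICER time point explicitly.

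A reader might infer more than the documents support:

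- **That baseline is ignored.** It is not: a difference score subtracts it. What is missing is the T1 score as a covariate.
- **That omitting site inflates false positives.** The effect runs the other way: the test becomes conservative.
- **That the study is underpowered.** At 64 per arm and ρ = 0.3 the change score has about 67% power by the same formula, but 64 is not the enrolment target.
- **That the 12-month effect is never tested.** The article says only that outcomes are measured at all three visits and describes no between-group comparison at T3. Uncertainty in that effect does enter the bootstrapped ICER and the acceptability curve. This study is also an add-on to a separate effectiveness trial whose plan is not shown and which may test T3.
- **That shared therapists inflate type I error by a known amount.** Team size and caseload are given ("Each team includes 3–5 therapists who have a caseload of 3–5 clients each"), but neither the number of teams nor an intraclass correlation is, so any figure would be assumed.
- **That the bootstrap ignores site, or that the within-group tests will be read as treatment effects.** The article does not say how the replicates are drawn, which an article may leave out. It also lists the within-group tests beside the between-group ones, without saying that a treatment effect will be inferred from them.

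**Conclusion.** The point holds as one of precision and consistency, not of bias. The mismatch between the tested interval (apparently T1–T2) and the 12-month effect in the ICER follows from the article's own text and needs no numerical assumption. The same is true of the mismatch between a possible rank test and a ratio of means.

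The cost of not adjusting for T1 depends on ρ, which is not given. ANCOVA variance is 15% to 35% lower for ρ from 0.7 to 0.3. At full enrolment and d = 0.5 on the raw-score SD, the gain is about 11 percentage points of power at ρ = 0.3 (0.960 − 0.848), 4 at ρ = 0.5 and under 1 at ρ = 0.7. The cost of omitting site depends on an assumed site share: at 10%, type I error is about 4% and the loss is about 3 points of power at d = 0.4 (0.843 − 0.816). The change should be made, since it improves a stated method with data already planned.

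**What to change.** Replace the between-group paragraph of Statistical analysis with a linear model adjusted for the T1 score and site. This can be ANCOVA at each visit, or a mixed model over T2 and T3 with arm, visit, arm by visit, T1 score and site.

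- Report the adjusted mean difference with its 95% CI at both T2 and T3.
- Name T3 as the contrast that feeds the ICER, and state that the 12-month effect is the T3 measurement, scheduled at about 11 months.
- If the data are skewed, use a bootstrap CI for the mean difference instead of a rank test, so that the effect analysis and the ICER share one estimand.

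The cost is a change of wording and a slightly more complex model. No new visits, participants or data are needed.

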### Outcome measures

In cost-effectiveness studies, costs are linked to treatment or clinical outcomes. All outcomes will be assessed at all three measurement moments.

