#### Costs items

In addition to change in primary outcomes, the costs of Multisystemic Therapy compared to CAU will be assessed. Cost assessment will be done from a societal perspective, over a time horizon of one year.

Cost components of adolescent antisocial behaviour will be measured by a modified version of the Trimbos/iMTA questionnaire for Costs associated with Psychiatric Illness (TiC-P) [24]. This questionnaire is originally designed to measure direct and indirect costs of mental health problems. For the current study, we adjusted the questionnaire to a version more suitable for assessments of costs related to child antisocial behaviour [25]. We did this mainly by adding items about youth and social care. Direct costs of the interventions as well as indirect costs will be assessed via various informants, namely professionals, parents and adolescents.

*Direct costs* concern use of all resources that is directly related to the intervention and will be estimated through the review of (time) investment of the professionals, including training, overhead, communication with relevant others, and time and travel costs of professionals involved. In addition, direct costs of health and youth care utilization will be assessed via parents (among other things: visits of the adolescent and parent to health and youth care professionals, hospitalizations and residential treatments, contact with judicial authorities and medication use).

*Indirect costs* are characterized as productivity losses, due to time lost from work because of the antisocial behaviour of the adolescent [26]. Data on productivity loss will be collected via the Short Form Health and Labour Questionnaire (SF-HLQ) that is part of the TiC-P [24]. The Short-Form HLQ (SF-HLQ) contains questions about absence from work, reduced efficiency at work and difficulties with job performance.

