The *valuation* section of the EQ-5D contains a visual analogue scale, on which the participant rates his/her health on a vertical, visual analogue scale where the endpoints are labelled ‘Best imaginable health state (score of 100)’ and ‘Worst imaginable health state (score of 0)’. Valuations of the VAS (original values 0–100) will be linearly transformed into a 0 to 1 score. This valuation of health status is a so-called ‘utility’, a relative valuation of a health condition compared with perfect health and dead. This method has been found to be efficient and easy to use, and appears to provide meaningful values for relative preferences of health and treatment [31]. Thus far the EQ5D has not been validated in the domain of behavioural problems, i.e. there are no formal utilities available for severe antisocial behaviour. In a separate study we have generated valuations for serious behaviour problems in children and adolescents ([name] et al., submitted).

The *SF-20* assesses six important health concepts: physical functioning, role functioning, social functioning, mental health, current health perceptions, and pain. Each dimension has five levels. For each subscale, a scale score will be calculated. The scale scores can be seen as multidimensional, health-related quality of life indicator. The internal consistency of the subscales of the Dutch SF-20 has proved sufficiently high: Cronbach's alpha for each subscale was at least .80 [32,33].

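### The cost-utility ratio sets a year of costs against an EQ-5D utility difference at one time point, so it is not comparable with a per-QALY threshold

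*Protocol article*

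**What the plan says.** - **Costs.** The Costs items section states: "Cost assessment will be done from a societal perspective, over a time horizon of one year". In Statistical analysis, for the cost-effectiveness analysis, "mean annual societal costs will be linked to the primary measure of effect", that is, aggressive and delinquent behaviour.
- **Cost-utility effect.** The same section adds: "A cost utility analysis will link the EQ-5d based utilities to the cost".
- **The ratio.** One rule covers both the cost-effectiveness and the cost-utility ratio. For the latter it reads that the "cost utility ratio (ICER) will be computed on complete cost-effect pairs by dividing the incremental societal costs by the incremental effects at 12 months".
- **Measurement times.** Outcome measures says: "All outcomes will be assessed at all three measurement moments". The abstract places these before treatment, then "immediately after treatment (T2; 5 months after T1) and at follow up (T3; 6 months after the end of the treatment".
- **EQ-5D scores.** Unit prices and cost calculations describes two scores. One is an index from the five dimensions, valued with the British tariff. The other is a visual analogue scale (VAS) divided down to a 0 to 1 range, with the best and worst health the respondent can imagine as its ends. The text then calls the VAS valuation a utility, "a relative valuation of a health condition compared with perfect health and dead".

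**The concern.** A utility is the value of a health state. It becomes an amount of health only when it is multiplied by the time spent in that state. The numerator of the ratio accumulates over a year, while the denominator, as worded, is a difference at one moment. What happens to utility between T1, T2 and T3 does not count, although it is measured.

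The article's stated purpose is to tell policy makers whether MST is worth its cost, using an acceptability curve over a range of threshold values. Thresholds for a cost-utility analysis are normally amounts per QALY. A reader who sets this ratio or curve against such an amount is comparing different units. The size and even the direction of the discrepancy depend on whether the effect grows, holds or fades by T3.

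This is more than detail left to a fuller document. The article states the formula, and a later plan that followed it would carry the mismatch forward.

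**Working it through.** The article gives no numerical cost-utility result, so there is no figure to reproduce. The check compares the denominator as written with a QALY difference on the trial's own schedule.

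**Inputs from the article.** T1 = month 0, T2 = month 5, T3 = 5 + 6 = month 11 (abstract). The ratio refers to month 12, so T3 = 12 is the alternative.

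**Assumptions, not in the article.** Utility is equal in the two arms at T1, so it does not matter whether the effect is a T3 difference or a difference in change from T1. The gain is 0.05 where a size is needed. Both denominators scale with the gain, so the ratios below do not depend on this choice.

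**Formula.** With x and y the differences between arms in utility at T2 and T3:

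- T3 at 11 months: QALY difference = [5·x/2 + 6·(x + y)/2] / 12
- T3 at 12 months: QALY difference = [5·x/2 + 7·(x + y)/2] / 12
- Denominator as written: y

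For a gain that is complete at T2 and kept (x = y = 0.05), T3 at 11 months gives (0.125 + 0.300)/12 = 0.0354, and 0.05/0.0354 = 1.41. T3 at 12 months gives (0.125 + 0.350)/12 = 0.0396, and 0.05/0.0396 = 1.26.

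| Assumed pattern | y | QALY, T3 at 11 | y/QALY | QALY, T3 at 12 | y/QALY |
|---|---|---|---|---|---|
| 0.05 by T2, kept | 0.05 | 0.0354 | 1.41 | 0.0396 | 1.26 |
| Linear growth to 0.05 at T3 | 0.05 | 0.0229 | 2.18 | 0.0250 | 2.00 |
| 0.05 at T2, half lost by T3 | 0.025 | 0.0292 | 0.86 | 0.0323 | 0.77 |
| 0.05 at T2, all lost by T3 | 0 | 0.0229 | ratio undefined | 0.0250 | ratio undefined |

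For linear growth, x = 0.05·5/11 = 0.0227 with T3 at 11 months, or 0.05·5/12 = 0.0208 with T3 at 12.

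**In money, for an assumed cost difference of 5,000 euro and T3 at 11 months.** With the gain kept, the written ratio is 5,000/0.05 = 100,000 euro per utility point, against 5,000/0.0354 ≈ 141,000 per QALY. With linear growth it is 100,000 against about 218,000. With half the gain lost it is 5,000/0.025 = 200,000 against about 171,000, so the discrepancy reverses.

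**The VAS.** If dead lies at position d on the 0 to 1 VAS, moving a score v to a scale with dead at zero gives (v − d)/(1 − d), which multiplies differences by 1/(1 − d). For an assumed d of 0 to 0.3 the multiplier is 1.00 to 1.43. This matters only if the VAS enters the ratio.

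**The case against.** The strongest defence is that one condensed sentence serves two ratios. For the behaviour scales an effect at the end of follow-up is normal, and the reference to 12 months may only name the horizon. An article may leave the construction of the utility effect to a fuller document. This explains how the wording may have arisen, but nothing in the text supports an accumulated effect, and the literal rule is a point-in-time denominator.

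Other parts of the defence stand, and they rule out stronger readings that a reader might infer:

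- **A broken promise of QALYs.** The article never uses the term. The fault lies in how the cost-utility effect is defined.
- **An acceptability curve with no valid axis.** A curve per utility point at one time can be drawn. It cannot be read against a per-QALY threshold.
- **A known bias in favour of MST.** The trajectories are assumed. Fading gains push the ratio the other way, and part of the 1.4 to 2.2 range comes from placing T3 at month 11. A zero denominator can also arise with a QALY-based ratio, but here it can arise when the QALY gain is not zero.
- **A cost-utility result spoiled by the VAS.** The article gives a British-tariff index and defends that tariff on grounds of comparability, which points to the index as the utility. It also admits that the EQ-5D is not validated for behavioural problems. The VAS label conflicts with the scale's own lower end, but it affects the ratio only if the VAS is used, which the text leaves open.
- **Damage to the main analysis.** Quality of life is not among the listed primary outcomes. The cost comparison and the ratios for aggressive and delinquent behaviour are untouched.

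**Conclusion.** The concern holds for the cost-utility ratio. As written, it is a year of societal costs per utility point at one time, not a cost per unit of health accumulated over that year, and it cannot be compared with a per-QALY threshold.

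For gains that build and persist, a reader who took it as a cost per QALY would understate that cost by a factor of about 1.4 to 2.2 (T3 at 11 months) or 1.26 to 2.0 (T3 at 12 months). For gains that fade, the cost per QALY would be overstated or the ratio undefined. These sizes rest on equal baselines, straight-line change between measurements and assumed trajectories. That the two quantities differ in kind rests only on the wording.

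This should be corrected before analysis. It is not a fatal flaw, because the analysis is not the primary one and the data needed are already to be collected.

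**What to change.** 1. Define the cost-utility effect as QALYs: the trapezoidal area under the British-tariff EQ-5D index over T1, T2 and T3.
2. Use the same time window for QALYs and costs, and reconcile the 11-month T3 with the one-year horizon. Either end both at T3, or state how both are carried to month 12.
3. Adjust the arm difference in QALYs for baseline utility. The T1 value enters the area with weight 5/(2·12) = 0.21, so a chance imbalance at T1 would otherwise pass into the effect.
4. Keep the end-of-follow-up effect for the behaviour scales only, with its time label matched to T3.
5. As a wording point, name the tariff index as the utility in the ratio and report the VAS as a descriptive health rating, since its zero is not dead.

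The cost is a few sentences in the analysis plan and a short calculation within each bootstrap replicate. All three EQ-5D measurements are already planned, so no new data collection is needed.

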#### Primary outcomes

Primary outcomes of this study include: recidivism and the frequency and seriousness of antisocial behaviour and other types of problems (internalizing problems, substance use). *Recidivism* will be assessed with data of the Research and Policy Database for Judicial Documentation. With this data we will assess the number of arrests, type and severity of offence of adolescents re-offending during the research period.

*Prevalence and seriousness of antisocial behaviour* will be assessed via different informants and instruments. First, parents and adolescents are asked to fill in the 33 items of the Delinquent Behaviour scale and the Aggressive Behaviour scale of the Child Behaviour Checklist (CBCL: 33 items) [19] and the Youth Self Report (YSR: 30 items) [20,21] respectively. For each item, the child’s behaviour has to be rated on a three-point scale, ranging from 0 (never) to 2 (often).

Additionally, adolescents will fill in two subscales of the Self-Report Delinquency scale (SRD) were used to assess self-report delinquency [22]. Adolescents will be asked to indicate on a list of potential delinquent behaviours whether they engaged in the described behaviours during the past 6 months (‘yes’ or ‘no’). The SRD ‘Violent offending’ (5 items) and ‘Property offences’ (10 items) scales will be used.

*Other types of problems* of the adolescent firstly comprise anxiety/depression, withdrawal and somatic complaints. These items will be measured with 25 items of the Youth Self Report [20,21].

In addition substance use (use of alcohol, soft and hard drugs) will be measured with several questions from a Dutch questionnaire used in the study Youth and risky behaviour [23].

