### Strengths and limitations

This study will contribute to the extension of scientific knowledge about economic evaluation in the field of child and youth care. This concerns the evaluation of the actual balance between costs and effects in a field of care where this has hardly ever been explored before, i.e. with very limited sources to derive costs of other outcome valuations from. The study will be conducted as part of a randomized controlled trial. By using such a design, it can be assumed that any confounding variables are cancelled out.

Furthermore, the study will be conducted as a multicentre trial. This will increase the generalizability of the study because this will lead to a large number of participants, different geographic locations and the ability to compare results among organizations. We will obtain both direct and indirect costs across the entire field of youth care. We will also include quality of life measures. To increase inclusion and prevent loss to follow up, all adolescents and parents will receive assistance in administering the questionnaires. Finally, most outcome variables will be assessed via two informants. Multi-informant assessment is recommended as a way to obtain a more complete picture of the adolescent than reliance on self- or parent-report alone [16].

Despite the strengths and innovative aspects of this cost-effectiveness study, there are some issues that our study is unable to take into account. First, follow-up is limited to a period of six months. To determine long-term effects of the intervention, there should be follow-up after a couple of years to assess the effects and costs when the adolescent is older. Second, it is to be expected that we will be dealing with a ‘difficult-to-reach”-population.

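### The base-case ICERs rest on complete cost-effect pairs in a population expected to be hard to reach; an all-randomised analysis using data already collected would be safer

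*Protocol article*

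**What the plan says.** The protocol article's Statistical analysis section fixes the set on which the ICERs are estimated: they "will be computed on complete cost-effect pairs", and the ratio is formed "by dividing the incremental societal costs by the incremental effects at 12 months". The same section adds: "Uncertainty around the ICERs will be estimated using bootstrapping, generating 5000 replications of the original dataset". The acceptability curve follows from this. Between-group effects are to be compared on pre-post difference scores.

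Assessments are at T1, T2 and T3 (Data collection procedure), and costs are taken over one year from a societal perspective (Costs items).

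Strengths and limitations says "it is to be expected that we will be dealing with a" population that is difficult to reach, and places this under the statement that "there are some issues that our study is unable to take into account". On prevention it says: "To increase inclusion and prevent loss to follow up, all adolescents and parents will receive assistance in administering the questionnaires". A payment of €10 per questionnaire is also planned. The article gives no dropout rate and describes no analysis that uses partly observed participants.

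Recidivism, by contrast, "will be assessed with data of the Research and Policy Database for Judicial Documentation", a source that does not depend on a completed follow-up questionnaire.

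**The concern.** A 12-month effect needs T3. A family with T1 and T2 data but no T3 has no complete pair, so it leaves the ICER, its bootstrap and the acceptability curve, even though two of its three assessments are in hand. What remains is a selected subset of those randomised. Bootstrapping describes sampling variation within that subset; it does not correct for who is absent.

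Strengths and limitations relies on randomisation to balance confounders. That protection covers everyone randomised, not those who happen to complete. The ICERs and the acceptability curve are the results policy makers are meant to use, so a shift in either part of the ratio matters.

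**Working it through.** **1. Is precision the problem?** Inputs from Sample size: effect 0.5 SD, power 0.80, alpha 0.05 (taken as two-sided).
- Plan's figure: n = 2(1.96 + 0.84)²/0.5² ≈ 63 per group by the normal approximation and 63.8 by the t-test, so the stated 64 is reproduced.
- Power with n complete pairs per arm is Φ(0.5·√(n/2) − 1.96). Out of 100 per arm, 19% loss leaves 81 (0.89), 30% leaves 70 (0.84) and 36% leaves 64 (0.81).

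The sample tolerates considerable loss on the planned effect. The issue is selection, not numbers.

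**2. Which kinds of loss bias the contrasts?** A simulation of 1,000,000 participants, with every parameter assumed: true T3 effect about −0.50 SD, about 20% loss overall, and skewed costs that rise with T2 and T3 severity. Effect is the MST − CAU difference at T3.

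| Loss depends on | Effect, all | Effect, complete pairs | Incremental cost, all | Incremental cost, complete pairs |
|---|---|---|---|---|
| Nothing | −0.50 | −0.50 | −€69 | −€68 |
| Arm only (27% CAU, 14% MST) | −0.50 | −0.50 | −€83 | −€81 |
| T1 severity, same rule in both arms | −0.50 | −0.50 | −€106 | +€179 |
| T2 severity, same rule in both arms | −0.50 | −0.47 | −€39 | +€538 |
| T2 severity, CAU only | −0.50 | −0.37 | −€34 | +€1,605 |

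Arm-only loss leaves both contrasts intact. Loss on T1 severity moves incremental cost by 179 + 106 = €285 but not the effect. Loss on T2 severity moves cost by 538 + 39 = €577, or by 1,605 + 34 = €1,639 when confined to CAU, and shrinks the effect.

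In the last three rows, regression on T1 and T2 returned the effect to about −0.50, and inverse-probability weights returned incremental cost to between about −€60 and −€110. The weights used the true loss model, so this is a best case. It does show that the discarded assessments carry usable information.

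**3. How large is it for the change scores the plan uses?** Assumptions: severity standard normal at T1 and T3 with correlation ρ; loss 15% under MST and 30% under CAU, log-odds slope 1 per SD; cost = exp(9.5 + 0.6 × T3 severity), mean about €16,000; no treatment effect.
- Among those observed, mean severity on the variable that drives loss is −0.133 (MST) and −0.253 (CAU), a gap of 0.120 SD.
- For a T3 score analysed without baseline, with loss on T3 severity, that gap is the bias: 0.12 SD.
- For the change T3 − T1, loss on T3 severity gives +(1 − ρ) × 0.120, and loss on T1 severity gives −(1 − ρ) × 0.120. At ρ = 0.4 this is 0.6 × 0.120 = 0.072; at ρ = 0.8 it is 0.2 × 0.120 = 0.024. Units are SDs of the score at one time point. The first case works against MST, the second in its favour.
- Incremental cost: with loss on T3 severity, mean observed cost is €14,502 (MST) and €13,383 (CAU), a false difference of about €1,120 against MST. With loss on T1 severity it is about €460 (ρ = 0.4) to €906 (ρ = 0.8).

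**The case against.** The strongest reply is that the document establishes neither the amount nor the pattern of loss. It gives no dropout rate, and hard to reach may refer partly to recruitment. It also plans face-to-face administration, payment, a Berber version and an Arab translator, besides help with the questionnaires. Imputation details are commonly left to an analysis plan that is not shown.

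Much of this stands, and it rules out several stronger readings that a reader might infer:
- **That MST families will be better retained.** CAU includes home-based services, FFT and MDFT, and in the North it is FFT. Nothing links interviews to the therapist. The 15% and 30% are assumptions.
- **That detained or placed youths, the costliest, drop out of the pairs.** Care use is collected from parents and the CBCL is parent-reported, so such a youth can still contribute costs and a CBCL score, though perhaps not a YSR.
- **That unequal loss by arm is enough for bias.** It is not, if loss is random within arm.
- **That the effect is biased by a quarter of the planned 0.5 SD.** The 0.12 SD in step 3 belongs to a final score without baseline, not to the planned change score.
- **That the cost difference and the ICERs will use different samples, or that the acceptability curve must widen.** The article defines no analysis set for the cost difference, and selection may shift the curve either way.

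What does not stand is the appeal to an unseen plan. Complete pairs are a choice stated in the article, not a gap, and an analysis plan that imputed for the base case would contradict it. The retention measures may reduce loss but do nothing for families who are lost.

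**Conclusion.** The point holds in a limited form. Naming complete pairs as the base case for the ICERs, and hence for the bootstrap and acceptability curve, discards partial follow-up in a population the authors expect to be hard to reach, and leaves the main economic result open to selection.

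Bias in incremental cost needs loss related to severity. Bias in both parts of the ratio needs loss related to post-baseline severity, or to severity differently in the two arms. Under the step 3 assumptions it is about 0.02 to 0.07 SD in the change score, of either sign, and about €450 to €1,150 in incremental cost. Other assumptions give other sizes (step 2), so these figures illustrate and do not predict. This is a cheap improvement, not an error that invalidates the design.

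**What to change.** Make the base-case ICERs and acceptability curve an analysis of all randomised participants. Impute wave-specific costs, utilities and CBCL/YSR scores by arm with multiple imputation, using T1 and T2 values, site and register-based recidivism as predictors, and combine this with the bootstrap. Use the same analysis set for the cost difference. Keep complete pairs as a sensitivity analysis, and add a scenario in which unobserved participants are costlier or more severe than their observed data predict.

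The cost is extra analysis work and no new data collection. The base case would then rest on a missing-at-random assumption, which cannot be verified (hence the added scenario) but is generally weaker than what complete pairs require.
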